### Study timeline

This trial began recruitment in August 2017. It is estimated to accomplish recruitment in November 2021 and complete the 6-month follow-up and data collection in May 2022. Figure 1 shows trial participation and study procedure.

**Fig. 1 Fig1:**
[figure not shown]
Flowchart of trial participation

### Randomisation, allocation concealment, and blinding

Allocation of participants in a 1:1 ratio to one of the two groups will be based on computer generated random numbers prepared by a statistician with no involvement in the trial. Block randomisation will be performed, stratified by study site and gender, given that hand OA disproportionately influences a larger number of females than males. The use of a central automated allocation procedure with security in place will ensure the allocation cannot be accessed or influenced by any person. Participants, assessors and statisticians will be blinded to group allocation. Allocation concealment and double blinding will be ensured by: (1) medications being dispensed by hospital clinical trial pharmacy at each site; (2) use of an identical placebo tablet; (3) subjective measures being taken by research assistants blinded to group allocation; (4) objective measures of structural progression being made by trained observers blinded to group allocation and time sequence of imaging. Emergency unblinding will be allowed in limited situations that impact on the safety of study participants. Code-break for the full randomisation schedule will be maintained by the administering institute. Tamper-proof unblinding envelopes, provided by the drug company preparing the study medication, will be used in case of the need for emergency unblinding. Participants who are unblinded will be withdrawn from treatment and be requested to complete questionnaires and have a follow-up hand x-ray and MRI scan at 6 months. Given the possible toxicities related to methotrexate, there is potential for investigators reviewing blood test results to become aware of treatment. Therefore, patient-reported outcomes will be assessed before any changes in dose or results of monitoring blood test are discussed with participants. The investigators with knowledge of blood test results will not be responsible for administering questionnaires.

### Intervention

Participants will be randomised to receive methotrexate (10 mg tablets) or placebo. Placebo will be manufactured to have same colour, taste and smell as methotrexate tablets.

#### Dosing

Methotrexate is currently used in rheumatoid arthritis, commonly dosed at 20 mg per week. Given that synovitis predates rapidly progressive radiographic hand OA [11, 12], and to alleviate concerns around inefficacy due to inadequate dosing, we will follow current guidelines for use of methotrexate in rheumatoid arthritis. The maximum dose will be 20 mg per week [30]. Participants will be prescribed 10 mg methotrexate or placebo weekly for four weeks, followed by 20 mg weekly for the remainder of the study if there is no toxicity as determined at the physician’s discretion (Australian Rheumatology Association Medication Information Sheets). The decision for dose escalation will occur at the 4-week physician review. If intolerances occur (e.g. nausea), the decision to increase to 20 mg weekly can be delayed until further clinical review. In a Cochrane systematic review of methotrexate monotherapy, 16% of people discontinued methotrexate within 52 weeks due to an adverse event, compared with 8% of placebo subjects [23]. All participants will be prescribed oral folic acid at a minimum dose of 5 mg per week, to be taken on days other than when methotrexate is taken. Folic acid supplementation has been shown to ameliorate side effects of methotrexate, as well as a significant reduction in discontinuation of methotrexate [31].

#### Safety

An independent data and safety monitoring board will be convened, consisting of two independent clinical rheumatologists, a clinical pharmacologist experienced in methotrexate use, and a biostatistician, all with clinical trial experience. They will monitor adverse events and will meet bimonthly and provide a written report to the chief investigators. Adverse events will be recorded throughout the study and chief investigators will be notified of any serious events within 24 hours. Safety of treatment will be assessed according to monitoring guidelines. As recommended by the Australian Rheumatology Association, full blood count, liver function test and urea and electrolytes tests will be performed at screening, 2, 4, and 8 weeks, 3 and 6 months (Australian Rheumatology Association, Patient Information: Methotrexate). If the results remain abnormal despite action (such as reducing the methotrexate dose), or at clinician discretion, then study medication will be stopped. Further reviews with a rheumatologist will be performed at 4 weeks, 3 and 6 months.

#### Compliance

Pill counts will be performed at each clinical assessment to document compliance. Weekly telephone contact for the first 3 months will be conducted to address any concerns, as well as regular clinical reviews with a study rheumatologist (at baseline, 4 weeks, 3 and 6 months). This will help to mitigate non-compliance.

#### Concomitant medication

To maintain the pragmatic nature of the trial, there are no restrictions with regard to concomitant analgesic medications. The participants will be allowed to continue taking the treatments that they are taking at their screening visit for the duration of the trial. If a participant is experiencing pain and requires an increase in the dose of analgesics, then the use of paracetamol, topical or oral NSAIDs or opioids, or a combination of these will be permitted, but the reason for the dose increase and the dose used will be documented. Trimethoprim, which interacts with methotrexate, will not be permitted.

### Study procedure

Table 1 shows the study procedure. Volunteers will be telephone screened before undergoing in sequential order (i) clinical assessment with a rheumatologist, chest x-ray and blood tests [full blood count, kidney function test, liver function test, C-reactive protein, erythrocyte sedimentation rate, rheumatoid factor, anti-cyclic citrullinated peptide antibodies, human immunodeficiency virus, Hepatitis B (sAb, sAg and cAb), Hepatitis C, and Quantiferon Gold] to assess the eligibility of the participants and ensure no contraindication to methotrexate; (ii) x-ray of both hands (standardized posteroanterior view) to confirm radiological disease; and (iii) MRI of the study hand to determine the presence of synovitis. Consent was obtained by study doctor. The symptomatic hand will be the study hand. In case of bilateral symptomatic hands, the most symptomatic hand will be the study hand. In the case of bilateral and equal symptoms, the dominant hand will be studied. Participants are able to withdraw at any time during the trial; the time and reasons will be recorded. If participants withdraw from the study, they will be requested to complete questionnaires (posted to the participants with return envelope) and have a follow-up hand x-ray and MRI scan at 6 months or end of study where possible.

**Table 1 Tab1:** Timetable and measures to be made

	Screening		Double blind period					
	Screening / baseline assessment	Post-screening	MRI & randomisation	Week 2	Week 4	Week 8	Months 3	Months 6
**Visit/phone contact**	**0**	**1**	**2**	**3**	**4**	**5**	**6**	**7**
**Informed consent**^**1**^	X							
**Blood tests**^**2**^		X						
**Safety blood tests**^**3**^				*X*	X	*X*	X	X
**Telephone follow-up**				*X*		*X*		
**Clinical visit**	X				X		X	X
**Hand x-ray**		X^a^						X^a^
**Chest x-ray**^**4**^		X						
**Hand MRI**			X					X
**Medical history including vaccination**	X						X	X
**Medications and allergies**^**1**^	X				X		X	X
**Employment and education**	X							
**Smoking**	X							
**Alcohol consumption**	X			*X*	X	*X*	X	X
**Marital status and parity**	X							
**Questionnaires**								
Hand VAS	X				X		X	X
AUSCAN, FIHOA, HAQ, MHQ	X						X	X
SF-36	X							X
Knee WOMAC, painDETECT	X							X
**Physical examination**								
Height, weight, waist and hip circumference	X							
Grip strength	X						X	X
Tender/swollen joint count^1^	X				X		X	X
Cardiovascular (including blood pressure), respiratory, abdominal, skin examination	X							
**Compliance and safety (AEs)**^**1**^				*X*	X	*X*	X	X
**Dispense medication**			X				X	
**Pill count**					X		X	X

*MRI* magnetic resonance imaging, *VAS* Visual Analogue Scale, *AUSCAN* Australian Canadian Osteoarthritis Hand Index, *FIHOA* Functional Index for Hand Osteoarthritis, *HAQ* Health Assessment Questionnaire, *MHQ* Michigan Hand Outcomes Questionnaire, *WOMAC* Western Ontario and McMaster Universities Osteoarthritis Index, *AE* adverse event

^a^Baseline and follow-up x-ray performed at the same centre using a standardized protocol

^1^To be performed/reviewed by study doctor

^2^Full blood count, kidney function test, liver function test, C-reactive protein, erythrocyte sedimentation rate, rheumatoid factor, anti-cyclic citrullinated peptide antibodies, human immunodeficiency virus, Hepatitis B (sAb, sAg and cAb), Hepatitis C, and Quantiferon Gold

^3^Full blood count, kidney function test, and liver function test

^4^Not required if chest x-ray in last 12 months is available

### Primary outcome

#### Pain reduction at 6 months

Pain reduction at 6 months will be measured according to the recommendations of the OARSI clinical trials for symptom modification in hand OA [28]. This taskforce recommended the use of a single question pain VAS as the main outcome measure for pain in hand OA clinical trials. In a recent systematic review, VAS was most frequently used for pain assessment in hand OA, with excellent reliability, good construct validity and sensitivity to change [32].

### Secondary outcomes

#### Change in pain and function at 6 months

At baseline and 6 months, hand pain, physical function, joint activity, and hand strength will be measured according to the OARSI recommendations of clinical trials for symptom modification in hand OA [28] using the Functional Index for Hand OA (FIHOA) [33], Australian Canadian Osteoarthritis Hand Index (AUSCAN) [34], Health Assessment Questionnaire (HAQ) [35], Michigan Hand Outcomes Questionnaire (MHQ) [36], Short-Form-36 (SF-36) [37], tender and swollen joint count [38], and grip strength.

#### Structural progression at 6 months assessed from MRI

Participants will undergo hand MRI for screening and a repeat MRI 6 months later using a 3.0 T or 1.5 T MRI unit according to local safety rules and standardised sequences across the 4 study sites. The participant will be positioned prone with their arm above their head with a positioning frame. Details of the sequences and parameters are shown in Table 2. Scan time is estimated at 20 minutes. Cartilage and bone will be assessed from coronal T1-weighted and proton density-weighted images. Synovitis and tenosynovitis will be assessed from coronal and axial proton density-weighted images. MRI at baseline and 6 months will be assessed using the OMERACT hand OA score (grades 0-3) for synovitis and bone marrow lesions [29]. Readings will be performed by trained observers blinded to clinical information, time sequence of MRIs, and group allocation. Progression of synovitis or bone marrow lesions will be defined as an increase in grade ≥ 1 from baseline to follow-up.

**Table 2 Tab2:** Magnetic resonance imaging sequences and parameters

	Machine	T1-weighted fat-saturated 3D gradient-echo acquisition, coronal	Proton density-weighted fat-saturated acquisition, coronal	Proton density-weighted fat-saturated acquisition, axial
**Melbourne**	3.0-T whole body MR unit (SIEMENS, Skyra)	repetition time 700 msec; echo time 12 msec; flip angle 120 degrees; field of view 24 cm; 512×352 matrix; pixel 0.43*0.43; slice thickness 0.5 mm	repetition time 2400 msec; echo time 65 msec; flip angle 150 degrees; field of view 24 cm; 640×440 matrix; pixel 0.375*0.375; slice thickness 2 mm	repetition time 4870 msec; echo time 50 msec; flip angle 150 degrees; field of view 14 cm; 160×320 matrix; pixel 0.41*0.41; slice thickness 2 mm
**Hobart**	1.5T whole-body MR unit (GE, Optima)	repetition time 700 msec; echo time 20 msec; flip angle 90 degrees; field of view 22 cm; 512×512 matrix; pixel 0.43*0.43; slice thickness 0.6 mm	repetition time 2400 msec; echo time 60 msec; flip angle 160 degrees; field of view 24 cm; 1024×1024 matrix; pixel 0.23*0.23; slice thickness 2 mm	repetition time 4870 msec; echo time 50 msec; flip angle 160 degrees; field of view 13 cm; 512×512 matrix; pixel 0.25*0.25; slice thickness 2 mm
**Adelaide**	3.0-T whole body MR unit (SIEMENS, Skyra)	repetition time 700 msec; echo time 12 msec; flip angle 120 degrees; field of view 22 cm; 512×408 matrix; pixel 0.43*0.43; slice thickness 0.5 mm	repetition time 2400 msec; echo time 54 msec; flip angle 150 degrees; field of view 22 cm; 640×520 matrix; pixel 0.34*0.34; slice thickness 2 mm	repetition time 4870 msec; echo time 42 msec; flip angle 150 degrees; field of view 18 cm; 512×416 matrix; pixel 0.35*0.35; slice thickness 2 mm
**Perth**	1.5-T whole body MR unit (SIEMENS, Aera)	repetition time 550 msec; echo time 11 msec; flip angle 120 degrees; field of view 24 cm; 512×360 matrix; pixel 0.47*0.47; slice thickness 0.5 mm	repetition time 2420 msec; echo time 60 msec; flip angle 150 degrees; field of view 24 cm; 640×520 matrix; pixel 0.375*0.375; slice thickness 2 mm	repetition time 4870 msec; echo time 48 msec; flip angle 150 degrees; field of view 14 cm; 220×320 matrix; pixel 0.44*0.44; slice thickness 2 mm

#### Radiographic progression at 6 months

Radiographs will be performed at baseline and 6 months with a standardised posteroanterior view with the beam focused on the head of the third metacarpal, using a hand map for reproducibility of position, as recommended by OARSI clinical trials for imaging in hand OA taskforce [39]. One reader will score radiographs according to the OARSI atlas for progression of hand OA [40], blind to clinical information, time sequence of x-rays, and group allocation. Our reproducibility is high (kappa 0.7 to 0.9) [41]. Progression will be defined by any increase in Kellgren and Lawrence grade in any joint as previously described [3] and recommended by the OARSI taskforce for outcomes in clinical trials of hand OA [39], for joints with synovitis and for both hands. This method is endorsed by a systematic review as the most valid, reliable and sensitive to change [42].

### Other measures

#### Descriptive data

Age, gender, height, weight, duration of symptoms, employment, medical history, medication use, marital status, education level, smoking, alcohol consumption, parity and menopausal status.

#### Adverse events, analgesic use, and co-interventions

These will be measured in a log-book and by structured questioning by the blinded assessor at each follow-up.

#### Biochemical parameters

General (cell counts, liver and renal function), inflammatory markers (C-reactive protein, erythrocyte sedimentation rate).

### Sample size calculation

The average VAS pain in a previous clinical trial of symptomatic hand OA similar to the proposed study was 54 mm (standard deviation 20 mm) [43]. The minimal clinically important difference to be detected in OA trials is a 15 mm change in VAS pain (out of 100 mm) [44]. We will require 38 participants in each group to attain a power of 90% to detect the minimal clinically important difference (alpha 0.05, two-sided significance). Accounting for an estimated 20% loss to follow-up, we will recruit 96 participants, 48 in each group.

### Statistical analyses

Analyses will be conducted in Stata v16 or later. An intention-to-treat analysis, including all participants in their randomised groups regardless of their adherence to assigned treatments, will be performed in a blinded fashion. The effect of intervention on pain reduction and other pain and function outcomes measured at multiple time points (for pain: week 4, month 3 and month 6; for secondary pain and function measures, month 3 and month 6) will be analysed using mixed linear regression models, with a random intercept for participant. Models will be adjusted for the baseline measure and the stratifying variables of site and gender, and include categorical terms for time, a term for randomised group and terms for the interaction between randomised group and time. Results will be presented as mean differences between groups at each time point with 95% confidence intervals, and p-values will also be reported. For measures only taken at baseline and a single follow-up time point, regression models will omit random intercepts and terms for time. Regression modelling assumptions will be assessed graphically. In the case of a gross departure from normality of residuals, ranked based techniques will be applied. As stipulated by OARSI clinical trial recommendations [28], binary logistic regression will be used to assess the effect of intervention on structural progression at 6 months, adjusted for the stratifying variables of site and gender. The outcome of tender/swollen joint count will be analysed via a Poisson model fit via generalised estimating equations with an exchangeable working correlation structure to account for multiple measurements per participant. This model will include the baseline measure and the stratifying variables of site and gender, and include categorical terms for time, a term for randomised group and terms for the interaction between randomised group and time. If more than 5% of participants are missing their primary outcome, multiple imputation will be applied to account for missing data, with missing values imputed separately by treatment group. Sensitivity analyses will fit outcome regression models additionally adjusted for age, body mass index, and severity of radiographic OA and synovitis if baseline imbalances between randomised groups with respect to these variables are considered clinically important. A sensitivity analysis of the primary outcome will be undertaken to estimate the effect of methotrexate under the assumption of hypothetical complete compliance to treatment by applying a two-stage least squares instrumental variables approach [45], where full compliance will be defined as participants taking at least 80% of their medication.

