**Methods:**

Ninety-six participants with hand osteoarthritis and synovitis will be recruited through the Osteoarthritis Clinical Trial Network (Melbourne, Hobart, Adelaide, and Perth), and randomly allocated in a 1:1 ratio to receive either methotrexate 20 mg or identical placebo once weekly for 6 months. The primary outcome is pain reduction (assessed by 100 mm visual analogue scale) at 6 months. The secondary outcomes include changes in physical function and quality of life assessed using Functional Index for Hand Osteoarthritis, Australian Canadian Osteoarthritis Hand Index, Health Assessment Questionnaire, Michigan Hand Outcomes Questionnaire, Short-Form-36, tender and swollen joint count, and grip strength, and structural progression assessed using progression of synovitis and bone marrow lesions from magnetic resonance imaging and radiographic progression at 6 months. Adverse events will be recorded. The primary analysis will be by intention to treat, including all participants in their randomised groups.

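### The primary mixed model, as stated, assumes equal variance and correlation at week 4, month 3 and month 6, so the month-6 standard error can be wrong in either direction

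*Protocol article*

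**What the plan says.** The abstract fixes one outcome and one time point: "The primary outcome is pain reduction (assessed by 100 mm visual analogue scale) at 6 months". The Statistical analyses section then models all three follow-up measurements together ("for pain: week 4, month 3 and month 6"). The outcomes measured repeatedly "will be analysed using mixed linear regression models, with a random intercept for participant". On the fixed part, "Models will be adjusted for the baseline measure and the stratifying variables of site and gender", and the models "include categorical terms for time, a term for randomised group and terms for the interaction between randomised group and time". On reporting, "Results will be presented as mean differences between groups at each time point with 95% confidence intervals".

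The section names no visit-specific residual variance, no random slope, no baseline-by-time term and no robust standard error for this model. Two safeguards are stated. One is general: "Regression modelling assumptions will be assessed graphically". The other says what happens next, but for one problem only: "In the case of a gross departure from normality of residuals, ranked based techniques will be applied". A working correlation structure is named only for the joint-count model.

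**The concern.** A random intercept with independent residuals of constant variance implies compound symmetry given the covariates: the same residual variance at each visit and the same correlation between any two visits. The standard error of the month-6 difference then uses the average residual variance over week 4, month 3 and month 6, not the month-6 variance. The single baseline slope adds a further constraint, because baseline pain may predict week 4 better than month 6.

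If residual variance at month 6 is above the average, the primary interval is too narrow and the test rejects too often. If it is below the average, the interval is too wide and power is lost. One contrast decides the trial, so its standard error should not depend on an assumption that the plan neither justifies nor protects.

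**Working it through.** **The plan's own figure.** With difference 15 mm, SD 20 mm, two-sided alpha 0.05 and 90% power: n = 2 × (1.960 + 1.282)² × 20² / 15² = 37.4, so 38 per group. Then 38 / 0.8 = 47.5, so 48 per group and 96 in total. This matches the Sample size calculation section and does not depend on the present point.

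**Inputs.** From the document: SD 20 mm, three follow-up visits, 48 per group, 20% loss. Assumed, because the document does not give them: the SD at each visit (σ_t), the baseline SD (σ_B) and the correlation of each visit with baseline (ρ_t).

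**Formula for complete data.** The slope on baseline at visit t is β_t = ρ_t σ_t / σ_B, and the common-slope model uses their mean, β̄. The residual variance at visit t is

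v_t = σ_t²(1 − ρ_t²) + (β_t − β̄)² σ_B².

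The true variance of the month-6 difference is about 2v₃/n per group. The model reports 2v̄/n, where v̄ is the mean of the three v_t. So model SE / true SE = k = √(v̄ / v₃), and type I error ≈ 2[1 − Φ(1.96k)]. With complete data the correlation between follow-up visits drops out of this contrast.

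*Constant SD 20, ρ = 0.65/0.50/0.40.* Slopes are 0.65, 0.50, 0.40, mean 0.517. v = 231 + 7.1, 300 + 0.1, 336 + 5.4 = 238.1, 300.1, 341.4. v̄ = 293.2. k = √(293.2/341.4) = 0.927. Type I error = 6.9%.

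*SD 18/20/22, σ_B = 15, ρ = 0.60/0.50/0.40.* Slopes are 0.720, 0.667, 0.587, mean 0.658. v = 207.4 + 0.9, 300 + 0.0, 406.6 + 1.1 = 208.2, 300.0, 407.7. v̄ = 305.3. k = √(305.3/407.7) = 0.865. Type I error = 9.0%.

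*Falling SD 25/22/20, σ_B = 20, ρ = 0.50 throughout.* v = 470.5, 363.0, 301.4. v̄ = 378.3. k = √(378.3/301.4) = 1.120. Type I error = 2.8%.

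In the first two cases nearly all of the effect comes from the first term of v_t. The common slope adds at most 7.1 to a variance of 238, so a baseline-by-visit term alone would not cure the problem.

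**Simulation.** Null trials, 48 per group, REML random-intercept model, z-test at month 6, 2,000 runs per scenario. Dropout is completely at random. Site, gender and multiple imputation are left out.

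| Assumed pattern | Type I, complete | SE ratio | Type I, 20% dropout | SE ratio |
|---|---|---|---|---|
| Compound symmetry, SD 20 | 5.6% | 0.99 | 5.3% | 1.00 |
| SD 20, decaying correlation | 7.1% | 0.93 | 6.7% | 0.91 |
| SD 18/20/22 | 8.8% | 0.87 | 9.6% | 0.85 |
| SD falling 25/22/20 | 3.0% | 1.10 | 3.0% | 1.13 |

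A month-6 ANCOVA on the same data stayed between 4.5% and 5.9%. Further runs with complete data, 38 or 48 per group and somewhat different assumed correlations gave 5.1% to 5.9% under compound symmetry, 6.3% to 7.5% at constant SD with decaying correlation, 9.3% to 9.7% for 18/20/22, and 2.8% to 4.8% for falling SDs. Participant-clustered robust standard errors on the planned model held type I error between 4.9% and 6.1%.

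**The case against.** **The text does not state independent, equal-variance residuals.** A random intercept can be combined with visit-specific variances or robust errors, and an analysis plan that is not shown might do so. This stands in part, and it is why the point is worded as holding with default residuals. But the protocol does state the random part and the fixed terms, and its only specific fallback addresses non-normality. The graphical check could reveal unequal variance, but nothing says what would follow.

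**The direction is not known.** A reader might infer that month-6 variance must be the largest, because entry requires pain of at least 40 mm and because dose changes and analgesic use accumulate. The documents do not support this. Baseline is a covariate here, and selecting on a covariate leaves the residual variance given that covariate unchanged under a normal model. Simulation agrees: at SD 18/20/22, type I error was 9.7% with the floor and 9.4% without. If methotrexate has no effect on pain, dose changes cannot spread pain scores. Freely adjusted analgesics could compress scores as easily as spread them.

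**The larger figures are assumed.** A reader might also take 9% to 10% as the error rate of this trial. It belongs to one assumed pattern of rising SDs. The document gives a single SD.

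**The full planned analysis was not simulated.** With 20% loss expected and a 5% trigger, multiple imputation is likely, and it was left out along with site and gender. This stands, and the remedy has to say how it works with imputation.

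**Conclusion.** The point holds in a limited form. The stated model rests the month-6 standard error on equal variance and correlation across visits, and no stated safeguard covers a breach. Randomisation keeps the month-6 estimate unbiased with complete data, and the sample size is unaffected. What can be wrong is the standard error, and with it the interval and p-value, in either direction.

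Under the assumed inputs, a nominal 5% test runs at about 6% to 7.5% with constant SD 20 and decaying correlation, 9% to 10% with SD rising from 18 to 22, 3% to 5% with falling SD, and close to nominal under compound symmetry. The algebra is certain. The size and sign in this trial are not, because the document gives no visit-specific SD and no correlation. The case for change is that an inexpensive alternative removes the dependence, not that the planned interval is known to be too narrow.

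**What to change.** For pain, replace the random intercept by an unstructured residual covariance over the three visits, fitted by REML with Kenward-Roger degrees of freedom, and add a baseline-by-visit interaction. The planned software can fit this: in Stata `mixed`, no random constant, `residuals(unstructured, t(visit))` and `dfmethod(kroger)`. With complete data and the same covariates allowed a separate effect at each visit, the month-6 estimate equals the month-6 ANCOVA, which held its level in the runs above. With missing visits it still uses the earlier data.

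At minimum, keep the planned model and use participant-clustered robust standard errors. Use the same form for the scales measured at months 3 and 6.

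Where multiple imputation is triggered, include all visits in the imputation model, fit the same analysis model in each imputed dataset and pool. Fix the choice before unblinding.

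The cost is wording and a line of code. The covariance has six parameters (three variances and three covariances) instead of two, and the interval is slightly wider if compound symmetry in fact holds.
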